### Independent variable: rehabilitation program

The rehabilitation program is identical in both randomised groups, and will be dispensed by physical therapists of the Clinique universitaire de réadaptation de l’Estrie (CURE). Only the delivery mode will differ; TELE group (in-home telerehabilitation) or CLINIC group (conventional face-to-face rehabilitation in a clinic). The intervention consists of a rehabilitation program with constant qualified physical therapist supervision. The exercise program, based on a post-prosthesis and post-fracture rehabilitation program developed by the orthopaedic surgery division of the CIUSSS de l’Estrie - CHUS, includes stretching, pain management, range of motion and muscular strengthening, in addition to a question period. An example of a rehabilitation session is described in Table 1. The attending physical therapist will also adjust the exercises according to the progression of each patient’s condition (see Table 2 for the rehabilitation session progression).

**Table 1 Tab1:** Example of a rehabilitation session

Length (minutes)	Exercise types
≈5 à 10	Warm-up and stretching
≈15 à 30	According to progression • Weeks 1–2 : Pain management and range of motions • Weeks 3–4 : Range of motion renewal (active assisted) • Weeks 5 à 8 : Range of motion maintaining (active) and muscle strengthening
≈5 à 10	Question period
Total : ≈ 30–45	End of the intervention

**Table 2 Tab2:** Rehabilitation session progression

Exercices	Weeks^a^							
	1	2	3	4	5	6	7	8
Circulatory movements	x	x						
Pendulum movements	x	x						
Wrist and elbow movements	x	x						
Thermal method (if necessary)	x	x	x	x	x	x	x	x
Range of motion exercices			x	x	x	x	x	x
Muscle strengthing					x	x	x	x

^a^Week 1 of rehabilitation matches to approximately week 3 post-fracture

The training program consisting of 30 to 45-min sessions, which will be realised for 8 weeks at a frequency of twice daily, either supervised (TELE or CLINIC) or unsupervised at home. During weeks 1, 3 and 5, patients will have to perform their exercises twice with direct supervision of the physiotherapist and others without this supervision. For the other weeks (2, 4, 6, 7, 8), patients will only have one supervised sessions, and the others without supervision. Supervised sessions will allow both the therapist and the patient to adjust the program if a problem occurs and assure the proper execution of the exercises.

#### Telerehabilitation technological platform

The originality of the in-home telerehabilitation intervention stems from the superior level and type of interaction between users (health care professional and patient), which exceeds the usual use of a videoconferencing system. As such, the technological support must be flexible in order to respond to the needs and constraints of such a system. The telerehabilitation platform used in this study was developed in collaboration with Vigilent Telesystems to address these issues. Figure 2 describes the telerehabilitation platform used in the study.

**Fig. 2 Fig2:**
[figure not shown]
Telerehabilitation technological platform. The patient and clinician systems include a 22″ touch monitor, a mini-PC (Intel NUC), a pan-tilt-zoom (PTZ) camera with embedded h264 video codec, a microphone array and a speaker. The telerehabilitation software, Vigil2, runs on both systems. The software includes functionalities for management (users, systems and sessions), patient status (online, offline, previous sessions, planned sessions), secure video, audio and data transfer over the Internet, and intuitive camera control (point-and-click control scheme). It also includes an easy way for the patient to turn on and off the system using the touch screen. Audio, video and sensor data coming from the patient’s home are transferred to the clinician using an application and database server over a secure link, allowing real-time sessions to occur

### Dependent variables

Participants will attend a total of two evaluations of approximately 1.5 h each with a trained research assistant at the Research Centre on Aging before (T1) and after (T2) the intervention period. Each assessment will be executed in the same order to optimise the validity of the collected information: 1) range of motion (flexion, extension, abduction, external and internal rotation); 2) upper limb function; 3) global shoulder function and pain; and 4) participant satisfaction. Every item will be evaluated at both assessments, except for the satisfaction, which will be assessed only at T2.

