## Methods/Design

### Study design

In our study, teletreatment will be used to provide physical therapy sessions from a service center (clinic) directly into the patients’ home. The study design is a RCT. As described in Fig. 1, there will be an evaluation at baseline (T1), 1 to 2 weeks post-fracture. Then, the 8-week intervention phase (telerehabilitation) or conventional rehabilitation in a clinic will begin at the moment prescribed by the orthopaedist, approximately 2 to 3 weeks post-fracture. Finally, a second evaluation (T2) will be held at the end of the intervention period.

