#### Range of motion

Shoulder range of motion (flexion, extension, abduction, and internal and external rotations) will be assessed by a universal goniometer [32]. This standard, simple and reliable instrument used to measure angles has a degree-graduated scale. Active and passive measurements will be taken with standardised procedures.

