#### Shoulder functional measures

Shoulder global function will be measured with the Constant score [36], which is the primary outcome measure. This questionnaire allows the assessment of four outcomes related to shoulder function: 1) pain; 2) activities of daily living (sleeping, work, leisure); 3) range of motion; and 4) muscle strength. The total is on 100 and a higher score indicates a higher shoulder function. According to a systematic review of the psychometric properties of the Constant score, the reliability of this questionnaire is excellent (ICC, 0.89; 95 % confidence interval, 0.79–0.94) [37], and the internal consistency, evaluated with the Cronbach alpha, ranges from 0.60 to 0.75 suggesting that it measures different aspects of function [38, 39].

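### The baseline visit calls for active motion and strength measurements about 4 to 6 weeks before the programme's own tables introduce either, and the article does not reconcile the two

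*Protocol article*

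**What the plan says.** **Timing.** Under Study design, "there will be an evaluation at baseline (T1), 1 to 2 weeks post-fracture". The intervention then "will begin at the moment prescribed by the orthopaedist, approximately 2 to 3 weeks post-fracture". The footnote to Table 2 adds: "Week 1 of rehabilitation matches to approximately week 3 post-fracture".

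**Content of T1.** Under Dependent variables: "Every item will be evaluated at both assessments, except for the satisfaction, which will be assessed only at T2". Satisfaction is the only exception named. Under Range of motion: "Active and passive measurements will be taken with standardised procedures". Under Shoulder functional measures: "Shoulder global function will be measured with the Constant score [36], which is the primary outcome measure". Its four parts are pain, daily activities, and "3) range of motion; and 4) muscle strength".

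**Staging of the programme.** Table 1 gives pain management and range of motion, with no mode stated, for weeks 1 to 2, and active-assisted motion for weeks 3 to 4. For weeks 5 to 8 it gives "Range of motion maintaining (active) and muscle strengthening". Table 2 marks range-of-motion exercises from week 3 and strengthening from week 5.

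**Uses of T1.** Statistical methods compares the groups at baseline, replaces missing data by extreme values (one of them being no change after the intervention), and computes cost per unit of change in the Constant score. The Discussion promises corrective measures if the groups differ at baseline.

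**The concern.** The assessment schedule asks a patient at T1 for movements that the exercise programme introduces weeks later. It neither makes an exception nor says what is recorded if a component is not performed. Two of the four parts of the primary outcome are involved, plus all active goniometry.

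An assessor facing a patient who does not perform the strength test could enter zero, leave the item blank, or rescale the remaining parts. These choices give different T1 totals for the same patient. A T1 total formed in mixed ways is a weak base for a change score, for an imputation that treats T1 as the T2 value, and for deciding whether the groups differ at baseline.

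**Working it through.** **1. The plan's own figure.** Inputs from Statistical methods: 26 per group, margin 10.3, SD 17, one-sided alpha 0.05.

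- Standard error = 17 × √(2/26) = 4.715
- 10.3 / 4.715 = 2.185
- Normal approximation: Φ(2.185 − 1.645) = Φ(0.540) = 70.5 %
- Noncentral t with 50 degrees of freedom: 69.5 %

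The stated 69 % is reproduced. No T1 quantity enters the calculation, so this point does not alter it.

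**2. Timeline in weeks after the fracture.** Programme week *k* begins at start + (*k* − 1), with the start at 2 to 3 weeks.

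| Event | Arithmetic | Weeks after fracture | Gap from T1 (1 to 2 weeks) |
|---|---|---|---|
| Week 3, active-assisted motion | 2 + 2 to 3 + 2 | 4 to 5 | 4 − 2 = 2 to 5 − 1 = 4 |
| Week 5, active motion and strengthening | 2 + 4 to 3 + 4 | 6 to 7 | 6 − 2 = 4 to 7 − 1 = 6 |

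Using the Table 2 footnote alone, programme week 5 is post-fracture week 7 and the gap is 7 − 2 = 5 to 7 − 1 = 6 weeks. The range of 4 to 6 respects both statements.

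**3. How firm each element is.** Both tables put strengthening at week 5. That active motion starts in week 5 rests on Table 1 alone, because Table 2 does not give the mode.

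**4. Where T1 scoring enters the analysis.** Let *d* be the amount by which one scoring convention lowers the T1 total relative to another, taken as equal in all patients.

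- *Comparison of T2 scores:* T1 does not enter, so there is no effect.
- *Difference in mean change:* *d* is added in both arms and cancels.
- *Cost per unit of change:* the ratio in an arm moves from C/Δ to C/(Δ + *d*), where C is mean cost and Δ mean change. If Δ is the same in both arms, the difference between the ratios moves from (C_TELE − C_CLINIC)/Δ to (C_TELE − C_CLINIC)/(Δ + *d*). It depends on the convention even though both arms were scored alike.
- *No-change imputation:* each imputed T2 value falls by *d*. With m missing values per arm and 26 analysed, the TELE minus CLINIC difference shifts by −*d* × (m_TELE − m_CLINIC)/26, which is zero when equal numbers are missing.
- *Baseline comparison:* a common *d* cancels. Inconsistent scoring between patients adds noise, and items at floor hide real differences.

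The article gives no data from which *d* could be sized.

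**The case against.** The strongest reply is that nothing here is contradictory. The tables list exercises, and Table 1 is presented as an example session. A single measurement is not a training stage, and no section forbids an active or strength test at T1. If a patient cannot raise the arm soon after a fracture, a low Constant score may describe that patient correctly, on the same scale as at T2. Trained research assistants, standardised procedures and calibrated assessors are mentioned, and a rule for unperformed items may stand in the full protocol.

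Much of this stands. A reader might infer that T1 testing is unsafe, that it cannot be done, or that the schedule and the programme cannot both be followed. The article supports none of these. Its Background reports early mobilisation favourably. The 3-day immobilisation study there was followed by passive mobilisation, so it does not settle active or strength testing either way. A reader might also see a conflict between Tables 1 and 2 over range of motion in weeks 1 to 2. That is arguable, since the pendulum, wrist and elbow movements in Table 2 may be what Table 1 means, and it has no bearing on T1.

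What does not fall is the stated rule. The article does more than leave out a detail: it says that every item but one is taken at both visits, and that wording sits unexplained beside staging that brings in the same movements weeks later. A scoring rule elsewhere would still leave this sentence in need of qualification.

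**Conclusion.** The point holds as a failure to reconcile the content of T1 with the programme's staging. As written, T1 takes active motion and strength about 4 to 6 weeks before the programme introduces them. This involves two of the four Constant parts and could concern any of the 52 participants. How many would be unable to perform a component is not known.

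It would be wrong to infer bias in the noninferiority comparison. T1 comes before randomisation, so the arms are affected alike. The article also does not say whether the primary test uses T2 scores or change, so it cannot be assumed that the primary test rests on the T1 total. The supportable consequence is narrower: a T1 Constant total that may be at floor, incomplete or inconsistently scored feeds the cost per unit of change, the no-change imputation, and the baseline comparison with its corrective measures.

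This rests on two assumptions: that the rule with its single exception is applied literally, and that no unpublished scoring rule already resolves it. The matter should be corrected, and correction is cheap.

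**What to change.** 1. Reconcile Study design, Dependent variables, Range of motion and Shoulder functional measures with Tables 1 and 2. The clinical team decides what is tested at T1; this review takes no view on that.
2. Amend the sentence that admits satisfaction as the only exception. State which Constant components are obtained at T1 and how an unperformed component is scored.
3. Compare the groups on the T2 Constant score with prespecified adjustment for the T1 measures actually obtained (for example pain, daily activities and DASH), in place of the unadjusted t-test named in the abstract. This also replaces corrective measures triggered by observed baseline differences.
4. If the T1 total is incomplete, form no change in the Constant total. Base the cost ratio on the between-group difference in T2 Constant, and define the no-change imputation from what was measured.

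**Cost.** A short clarification or amendment. The baseline covariate may predict T2 less well than a complete score would. The economic ratio must be re-expressed if no T1 total is formed. In a noninferiority trial the T2 difference may lie near zero, which makes a ratio unstable, so the cost difference and the T2 difference should also be reported side by side.

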#### Range of motion

Shoulder range of motion (flexion, extension, abduction, and internal and external rotations) will be assessed by a universal goniometer [32]. This standard, simple and reliable instrument used to measure angles has a degree-graduated scale. Active and passive measurements will be taken with standardised procedures.

#### Upper limb function

Shoulder function will be evaluated with the the Disability of the Arm, Shoulder and Hand questionnaire (DASH) [33]. This self-administered questionnaire includes 30 questions evaluated on a 5-point Likert scale, most of which relate to the individual’s capacity to realise a task. This tool was chosen for its scientific validity, ease of use, and ability to accurately reflect activity levels in daily living. The result is on a total of 100, where a high score indicates a greater disability. The original English version questionnaire demonstrated a good test-retest reliability (intraclass correlation coefficient = 0.95), a good internal consistency (Cronbach alpha = 0.96) and a moderate construct validity according to Spearman correlations varying from -0.58 to -0.76 [34]. However, factorial analyses demonstrated that five factors explained 67 % of total variance [35].

#### Shoulder functional measures

Shoulder global function will be measured with the Constant score [36], which is the primary outcome measure. This questionnaire allows the assessment of four outcomes related to shoulder function: 1) pain; 2) activities of daily living (sleeping, work, leisure); 3) range of motion; and 4) muscle strength. The total is on 100 and a higher score indicates a higher shoulder function. According to a systematic review of the psychometric properties of the Constant score, the reliability of this questionnaire is excellent (ICC, 0.89; 95 % confidence interval, 0.79–0.94) [37], and the internal consistency, evaluated with the Cronbach alpha, ranges from 0.60 to 0.75 suggesting that it measures different aspects of function [38, 39].

#### Patients’ satisfaction

Every patient will complete the French version of the validated Healthcare Satisfaction Questionnaire at T2 to evaluate their general satisfaction toward the health care service received [40]. This questionnaire also showed a good internal consistency (Cronbach’s alpha coefficient of the overall scale = 0.92) [40]. Satisfaction construct is determined by three distinct factors, whether satisfaction with the: 1) relationship with the healthcare professional; 2) services delivered; and 3) general healthcare organization. A score on 100 is computed for the general satisfaction, as well as for satisfaction of each domain.

In addition, patients’ satisfaction toward teletreatment (only for the TELE group) will be measured after removal of the technology by the technician using the Telemedicine Perception Questionnaire [41]. This validated questionnaire includes 14 items placed on a five-point Likert scale (where 1 = totally disagree and 5 = totally agree) for a total score of 56. The first six items explore the communication quality between the professional and the patient, and the other items concentrate on the patient’s perception of the quality of the received service, including coherence, accessibility and needs met.

#### Costs

Economic analyses are based on the health system perspective [42]. A grid previously developed and already used to collected costs associated to teletreatment (TELE group) and conventional rehabilitation (CLINIC group) for our post-knee arthroplasty [43] will also be part of this study.

### Statistical methods

The principal analyses intend to test the noninferiority of the TELE intervention versus the CLINIC intervention. We aim to recruit a total of 52 participants, or 26 participants per group. Sample size was determined with data from a previous study on the Constant score [44], which is considered in this study as the primary outcome measure. With 26 participants per group, within the context of a unilateral t-test with an alpha level set at 0.05, the power of the study to reject non-equivalence hypothesis would be at 69 % for a difference of 10.3 or less (standard deviation = 17). This noninferiority point is under the minimal clinically important difference of 10.4 points on the Constant score [44].

Participant characteristics in each group will be described pre-intervention (T1) using mean and standard deviation (continuous variables) or proportion (categorical variables). Groups at baseline will then be compared using *t*-test or chi-squared test.

First, the data will be analysed according to the received intervention (per protocol), and then, according to the assigned group (intention to treat analysis). A sensitivity analysis will be used to explore the effect of compliance or screen failures: missing data will be replaced by extreme data (no change following intervention or most favorable change noted in the study). Any non-robustness of the revealed results by comparison of strategies will be noted.

Economic analysis is of cost-efficacy type. Cost by change-unit of the principal dependant variable (Constant score) will be determined for both groups. Differential cost will then be established.

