**Methods/Design:**

In this randomized controlled trial, individuals who have had a proximal humerus fracture treated conservatively at the Centre intégré universitaire de santé et de services sociaux de l’Estrie - Centre hospitalier universitaire de Sherbrooke (CIUSSS de l’Estrie CHUS), and who are returning home will be included. Participants will be recruited during their visit to the emergency ward or outpatient clinic by the medical or research team and will then sign the informed consent form if they are interested to participate in the study. We expect to recruit 52 participants (26 per group). Randomization will be done by a random number generator with sealed envelopes. Each patient will be evaluated before the beginning of the rehabilitation (T1), and immediately after the 2-month intervention (T2). The following outcomes will be measured: 1) upper extremity function (Constant Shoulder Score and Disability of the Arm, Shoulder and Hand questionnaire [DASH]); 2) range of motion (conventional goniometer); 3) user satisfaction (Health Care Satisfaction questionnaire); and 4) cost of services to the public healthcare system.

The difference between the two groups will be compared using a *t*-test or a chi-squared test, and through a cost-effectiveness economic analysis.

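### The analysis labelled per protocol groups patients by treatment received (as-treated), and no rule says which result decides noninferiority if it disagrees with intention to treat

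*Protocol article*

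**What the plan says.** All of this is in the Statistical methods section of the protocol article.

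- Aim: "The principal analyses intend to test the noninferiority of the TELE intervention versus the CLINIC intervention".
- Order and definition of the analyses: "First, the data will be analysed according to the received intervention (per protocol), and then, according to the assigned group (intention to treat analysis").
- Next comes a robustness check, in which "missing data will be replaced by extreme data (no change following intervention or most favorable change noted in the study").
- On disagreement: "Any non-robustness of the revealed results by comparison of strategies will be noted".
- Design figures: "We aim to recruit a total of 52 participants, or 26 participants per group", a test set "within the context of a unilateral t-test with an alpha level set at 0.05", and power that "would be at 69 % for a difference of 10.3 or less (standard deviation = 17").

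The primary outcome is the Constant score (Shoulder functional measures). The article gives no adherence criterion for the per-protocol label, describes no route for changing arm and gives no expected number of switchers.

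**The concern.** The sentence sets intervention received against group assigned. That contrast defines an as-treated analysis. A per-protocol analysis keeps every patient in the randomised arm and leaves out those with major deviations. An analyst who follows the words rather than the label would count a TELE patient who ends up in clinic visits as a CLINIC patient. If such patients are doing poorly, the move raises the TELE mean and lowers the CLINIC mean, and both changes favour noninferiority.

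The second gap compounds the first. In a noninferiority trial, treatment-based and assignment-based analyses can err in opposite directions, so the plan has to say which one decides or that both must pass. Here a conflict is to be reported, but nothing says what then happens to the trial's main conclusion.

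Switching is conceivable. Only the evaluator is blind (Participants), the exercise program is the same in both arms and comes from therapists of the same clinic (Independent variable: rehabilitation program), and TELE needs working equipment and internet in the home.

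**Working it through.** **1. The plan's own figure.** Inputs from Statistical methods: 26 per arm, SD 17, margin 10.3, one-sided alpha 0.05. True difference taken as 0.

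- Standard error = 17 × √(2/26) = 4.715.
- Noncentrality = 10.3 / 4.715 = 2.185, with 50 degrees of freedom.
- Power = 69.5% by the noncentral t (70.5% by the normal approximation).

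The stated 69% reproduces. The planned test is therefore a one-sided test against a 10.3-point margin, and the sample-size figure is not at issue.

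**2. How as-treated grouping moves the estimate.** Assumptions, not from the article: *k* TELE patients switch to clinic care, they score *w* points below the other TELE patients, and the true deficit as randomised is exactly 10.3. Set the mean of the randomised CLINIC arm to 0.

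- TELE patients who stay: mean = -10.3 + *kw*/26.
- Switchers: that mean minus *w*.
- CLINIC as treated: *k* × (switchers' mean) / (26 + *k*).

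| | *k* = 2, *w* = 10 | *k* = 3, *w* = 15 |
|---|---|---|
| TELE stayers | -10.3 + 20/26 = -9.53 | -10.3 + 45/26 = -8.57 |
| Switchers | -19.53 | -23.57 |
| CLINIC as treated | 2 × (-19.53)/28 = -1.40 | 3 × (-23.57)/29 = -2.44 |
| As-treated difference | -9.53 + 1.40 = -8.13 | -8.57 + 2.44 = -6.13 |
| Difference with switchers excluded | -9.53 | -8.57 |
| Intention-to-treat difference | -10.3 | -10.3 |

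**3. False noninferiority under the same assumptions.** Simulation with at least 20,000 trials per scenario, pooled t-test against -10.3, one-sided 5%. Ranges cover repeated runs.

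| TELE to CLINIC switchers | As treated | Intention to treat | Switchers excluded |
|---|---|---|---|
| None | 5.0% | 5.0% | 5.0% |
| 1, 10 points worse | about 7.5% | 4.9% | not needed |
| 2, 10 points worse | 10.6–11.2% | about 5% | about 7% |
| 3, 15 points worse | 19.4–20.1% | 4.6–5.0% | about 10% |

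In the last row, about 15% of trials pass as treated and fail by intention to treat, which is the conflict the article leaves open. Requiring both intention to treat and the exclusion-based per-protocol set to pass gives about 4.5%.

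**4. Other assumptions about switching.**

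- *Opposite direction.* If the same poor-prognosis patients move from CLINIC to TELE, as-treated false noninferiority falls below nominal: 3.4% (2 switchers, 10 points worse) and 1.9% (3 switchers, 15 points worse).
- *Switchers gain the benefit of clinic care.* Here the deficit of 10.3 attaches to treatment received, and the 3 TELE patients with the worst prognosis switch. With a correlation of 0.5 to 0.8 between prognosis and outcome, false noninferiority is 16.0–27.2% as treated, 10.1–15.2% with switchers excluded and 8.3–8.8% by intention to treat. The as-treated analysis passes while intention to treat fails in 8–18% of trials.
- *Switching unrelated to prognosis*, same model, 1 to 5 switchers: 4.7–5.3% as treated, and 6.0–10.4% by intention to treat.

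No single analysis is safe in every case, so a rule combining two sets is needed.

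**The case against.** **The text gives an order, not a ranking.** It never calls the received-intervention analysis primary. A reader might infer that noninferiority will be claimed from it even when intention to treat fails. The article does not say that, and running both analyses is sound practice for noninferiority. This objection stands. What remains is that neither analysis, nor both together, is made decisive.

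**The authors may have meant patients who received what they were assigned.** The parenthetical label points that way, and nothing says explicitly that a switcher is moved. But the wording sets received against assigned and supplies no adherence criterion, so the literal reading is as-treated. An ambiguity in a principal analysis still needs correcting.

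**Set definitions and decision rules usually belong in the statistical analysis plan.** True in general, and a rule may exist there. The article, however, itself fixes the grouping and the handling of disagreement, and a plan faithful to it would inherit both. The sentence on non-robustness directly follows the missing-data analysis, so strategies may mean partly those replacements. In that case the article says even less about a conflict between the two principal analyses.

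**The size rests on assumed switching.** This also stands. Number, direction and prognosis of switchers are not in the article. The travel barrier it describes in the Background could even favour movement towards TELE.

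**Conclusion.** The point holds in a limited form. An as-treated grouping carries a per-protocol label, and no rule settles a conflict with intention to treat. If poor-prognosis TELE patients switch to clinic care, two or three of 26 are enough to raise the as-treated false noninferiority rate from 5% to about 11% or 20%. Those figures assume SD 17, a true deficit of exactly 10.3 and switchers scoring 10 or 15 points worse.

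Two stronger readings are not supported. One is that the plan's type I error generally exceeds 5%. With no switching all analyses coincide, with the opposite direction the as-treated analysis is conservative, and with random switching it is intention to treat that is inflated. The other is that the trial will be judged by a test of difference, because the abstract says "The difference between the two groups will be compared using a *t*-test or a chi-squared test". The abstract is a summary across outcomes, while Statistical methods specifies a one-sided test against a margin, and the stated power matches that test.

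This should be fixed. It does not invalidate the design, since intention to treat is already planned and disagreement would be reported.

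**What to change.** Amend Statistical methods, or state in the analysis plan before unblinding:

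1. Intention to treat: all randomised patients, analysed in their assigned arm.
2. Per protocol: the subset who received their assigned intervention without major deviations, defined in advance and analysed in the assigned arm. Switchers are excluded and never moved to the other arm.
3. Decision rule: declare noninferiority only if the lower limit of the two-sided 90% confidence interval for TELE minus CLINIC on the Constant score is above -10.3 in both sets. This matches the planned one-sided 5% test.
4. Any analysis by treatment received is descriptive only.

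The joint rule matters because excluding switchers alone still leaves about 10% false noninferiority with 3 switchers 15 points worse. It does not guarantee 5% everywhere. Where switchers gain the benefit of clinic care, intention to treat by itself reached 8.3–8.8% with 3 prognosis-related switchers, and the joint error cannot exceed that.

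The cost is wording, with no new data or patients, and a slightly lower chance of claiming noninferiority. As a guide, at a true difference of 0 and with 1 to 5 switchers, requiring both the as-treated and the intention-to-treat analyses to pass gave power of 68.5–70.4% under prognosis-related switching and 60.9–66.4% under random switching, against about 69.5% with none. The recommended pair was not run for power.
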